## Abstract

**Background:**

Nutritional treatment is one of the most important components of multidisciplinary anti-cancer therapy. Home enteral nutrition is considered as a safe procedure, however, it may be associated with the risk of side effects, such as nausea, vomiting, abdominal pain, and diarrhoea. It is uncertain whether diarrhoea is the result of the enteral formula administration or gut dysbiosis. One of the methods which may be used to alter the composition of gut microbiota is the administration of a probiotic strain. *Lactobacillus plantarum* 299v ingestion was found to diminish the adverse events of irritable bowel syndrome and *Clostridium difficile* infection - entities that share the symptoms with enteral nutrition side effects. Therefore, the primary aim of this study is to determine the effect of *Lactobacillus plantarum* 299v on prevention of weight loss of cancer patients receiving home enteral nutrition. The secondary aims are to evaluate the role of this probiotic strain in the improvement of nutritional status, enteral nutrition tolerance, and patients’ quality of life.

**Methods:**

Forty patients with cancer receiving home enteral nutrition will be enrolled in this clinical trial and randomized to receive one capsule of *Lactobacillus plantarum* 299v (Sanprobi IBS®) twice a day or placebo for 12 weeks in a double-blind manner. Laboratory tests (the level of albumin, total protein, transferrin, and total lymphocyte count), anthropometric parameters (body mass, the content of fat mass, muscle mass, and total body water), Nutritional Risk Screening (NRS 2002), enteral nutrition tolerance as well as quality of life will be measured. Measurements will be obtained at the baseline and after 4 and 12 weeks of treatment.

**Discussion:**

The adverse events observed during administration of enteral nutrition have an negative impact on enteral formula tolerance and as a consequence patients’ quality of life. The previous studies have demonstrated that probiotics may reduce the gastrointestinal symptoms related to enteral nutrition. Thus, administration of *Lactobacillus plantarum* 299v may be effective in improvement of nutritional status, enteral nutrition tolerance, and quality of life of cancer patients receiving home enteral nutrition.

**Trial registration:**

ClinicalTrials.gov Identifier: NCT03940768.

## Background

Nutritional treatment is essential within the complexity of anti-cancer therapy. The appropriate nutritional support improves nutritional status, clinical outcomes, and as a consequence patients’ quality of life [1]. Home enteral nutrition (HEN) is recommended for patients with an efficiently functioning gastrointestinal tract who do not require hospital stay [2]. According to the Villar Taibo et al. trial, almost 75% of patients qualified for HEN are malnourished [3]. Moreover, it is estimated that around half of patients with malignancies eventually develop cancer cachexia [4, 5]. As it was stated above, HEN provides many benefits, however, it is associated with the risk of adverse events, mainly diarrhoea, nausea, vomiting as well as abdominal pain [2]. The frequency of diarrhoea varies, notwithstanding, it is estimated that it affects as much as 95% of patients receiving enteral nutrition (EN) depending on medical condition and the definition of diarrhoea being a multifactorial etiology [6]. Therefore, it should be considered whether diarrhoea is the side effect of EN (for instance – it is mainly caused by the unadjusted speed of the enteral formula administration) or it is caused by alterations in the composition as well as the activity of gut microbiota. The qualitative and quantitative changes in gut microbiota commonly referred as gut dysbiosis may occur in cancer patients [7]. It was elegantly shown that there are at least several factors contributing to the development of gut microecological niche imbalance among patients suffering from malignancies, mainly infectious and anti-cancer agents, antibiotics as well as poor eating habits [7, 8].

Currently, several therapeutic methods are used to alter the gut microbiota, predominantly administration of prebiotics, probiotics, synbiotics, and faecal microbiota transplantation [9, 10]. Probiotic strain – *Lactobacillus plantarum* 299v (*L. plantarum* 299v) is able to reside the human colonic mucosa in vivo due to a specific mechanism of mannose adhesion [11, 12]. It demonstrates high tolerance to acidic and alkaline environment of the stomach and the duodenum, respectively. Therefore, this probiotic strain survives transit through the gastrointestinal tract to the colon, where it can modify gut microbiota [8, 11, 12]. *L. plantarum* 299v provides anti-bacterial activity against potential pathogenic agents, such as *Listeria monocytogenes*, *Yersinia enterolytica*, *Enterobacter cloacae*, *Enterococcus faecalis* and *Escherichia coli*. It increases transcription of the genes encoding mucins (MUC2 and MUC3) and their secretion from goblet cells [13]. *L. plantarum* 299v has immunomodulatory properties reducing the pro-inflammatory cytokine synthesis and increasing the anti-inflammatory IL-10 production and secretion. This probiotic strain plays a supportive role in the treatment of irritable bowel syndrome (IBS), which was confirmed in Niedzielin et al. trial [14]. The participants were divided into two groups: first receiving probiotic (*n* = 20) in dose 200 ml (5 × 10^7^ CFU/ml) twice a day for 4 weeks and second consuming placebo (n = 20). All the participants from probiotic group declared a resolution of abdominal pain, while only 11 subjects from control group experienced relief (*p* = 0.0012). The normalization of stool frequency was most commonly observed in probiotic group in comparison to placebo (*p* = 0.17). Moreover, the improvement of all symptoms of IBS was noted in 95% subjects receiving probiotic and in 15% participants from control group (*p* < 0.0001) [14]. It should be emphasized that patients receiving HEN often develop similar gastrointestinal symptoms resembling IBS [2]. Limited data exists regarding the use of *L. plantarum* 299v in cancer therapy and no trials about its use in patients with cancer receiving HEN. The present randomized, double-blind and placebo-controlled study hypothesizes that administration of *L. plantarum* 299v might improve nutritional status, enhance the EN tolerance and quality of life (QOL) of patients with cancer who receive HEN.

## Methods

### Study aims

The primary aim of the study is to determine the effect of *L. plantarum* 299v on prevention of weight loss of patients with cancer receiving HEN. The secondary aims include the role of *Lactobacillus plantarum* 299v in the improvement of nutritional status, EN tolerance, and QOL of patients with cancer receiving HEN.

### Study design

In this 12-week, single-centre, randomized, double-blind, and placebo-controlled study, 20 patients with cancer will be treated with probiotics and 20 patients will receive a placebo. The post-allocation clinical and laboratory assessment will be performed at weeks 0, 4, and 12 in all participants (Table 1). Patients in the probiotic group will receive two capsules of Sanprobi IBS® containing 10^10^ CFU of *L. plantarum* 299v for 12 weeks. Participants in the control group will receive placebo (two capsules daily) for 12 weeks. The participants will be recruited to this study by the nutritionist and the surgeon in Nutritional Counselling Centre Copernicus in Gdansk and Medical University of Gdansk (Department of Clinical Nutrition and Dietetics). The researches and participants will be blinded to the group assignment since the probiotic product and the placebo will be completely identical and indistinguishable from one another. The enrolment of participants is presented in Fig. 1.

**Table 1 Tab1:**
[figure not shown]
Schedule of enrollment, interventions, and assessments.

**Fig. 1 Fig1:**
[figure not shown]
Participants flow diagram

### Subjects

#### Inclusion criteria

Patients will be included if they meet all of the following criteria:
Age ≥ 18 yearThe presence of cancerArtificial access to the gastrointestinal tract (naso-gastric tube, gastrostomy, percutaneous endoscopic gastrostomy, jejunostomy, percutaneous endoscopic gastrostomy with jejunostomy) – enteral feedingQualification for HENwritten consent to take part in the study

#### Exclusion criteria

Patients will be excluded if they meet any of the following exclusion criteria:
Qualification for home enteral nutrition, but suffering from another disease than cancerPatients requiring additional parenteral nutritionNot being able to visit the study centre

### Allocation to treatment, randomization, and blinding

At the beginning, the patients will have to sign an informed consent to participate in the study. After meeting all the inclusion criteria and obtaining a consent agreement, the participants will receive a unique number by the nutritionist. Each number will be allocated to particular intervention group. The eligible patients will be allocated to the treatment for 12 weeks with either to probiotic group or placebo.

Randomization will be performed by means of randomizer.com software, typically used by clinical research associates. The randomization ratio will be 1:1. The researches and participants will be blinded for treatment received from the probiotic company. The patients will intake one capsule of study product (probiotic or placebo) in the morning after breakfast and one capsule in the evening after dinner. The participants who cannot swallow the capsule, will be instructed to mix the capsules’ powder with 20 ml of water or saline and administer the solution through the enteral feeding access. The capsules (probiotic product as well as placebo) will be stored at refrigerator temperature.

#### Intervention group

The intervention group will be administered with Sanprobi IBS® capsule twice a day for 12 weeks. Each capsule contains 10^10^ CFU of *L. plantarum* 299v. The intervention capsules will be produced and packed by Sanprobi company (Sanprobi IBS® Sanprobi Sp. z o.o., Sp. k., Szczecin, Poland; producer of capsules – Institute Rosell-Lallemand, Montreal, Canada; LP299v owner of probiotic strain – Probi AB, Lund, Sweden).

#### Control group

The control group will receive placebo capsules twice a day for 12 weeks. The placebo capsules will be produced and packed by the same company (Sanprobi) as intervention capsules and it will not contain any microorganisms. One capsule of placebo 410 mg +/− 7.5% of contents, including potato starch – 403 mg and 7 mg of magnesium stearate (magnesium salts of fatty acids).

### Outcomes

#### Primary outcome

The primary outcome is the prevention of weight loss in a probiotic-receiving group in comparison to a placebo-receiving group.

#### Secondary outcomes

First secondary outcome is the improvement of nutrition status in patients receiving probiotic in comparison to placebo-receiving group. The nutritional status will be evaluated by means of anthropometric parameters (body mass index, fat mass, muscle mass, total body water), laboratory tests (the level of albumin, total protein, transferrin, total lymphocyte count) and Nutritional Risk Screening 2002 (NRS 2002 tool). Second secondary outcome is to estimate the differences of enteral nutrition tolerance in patients receiving placebo or probiotic supplements. Third secondary outcome is to evaluate the difference of QOL of patients receiving placebo or probiotic supplements.

### Data collection

#### Participant timeline

The timetable of follow-up visits and measurements is presented using The Standard Protocol Items: Recommendations for Interventional Trials (SPIRIT) diagram in the Table 1. Each of the participants will visit the study centre three times (at baseline, after 4 weeks, and after 12 weeks). During follow-up visits, patients will receive study products depending on allocation. At baseline – 60 capsules for 30 days; after 4 weeks – 120 capsules for next 60 days. If during this trial, any participant fails to continue the study protocol, the data will be collected and this information will be further noted in the publication.

#### Blood sampling and preparation

The level of albumin, total protein, transferrin, and total lymphocyte count will be measured. The blood samples will be taken from a forearm vein by a nurse at the baseline, after 4 weeks, and next after 12 weeks. All blood samples will be taken in Counselling Nutritional Centre Copernicus in Gdansk and the same day they will be given to the laboratory to conduct the analysis.

#### Anthropometric parameters

The analysis of the body mass composition (fat mass, muscle mass, total body water) will be conducted using a BIA analyser – Medical Jawon. It will be performed by a nutritionist in the Department of Clinical Nutrition and Dietetics (at baseline, after 4 weeks, and after 12 weeks). The body mass index will be also calculated by the nutritionist.

#### NRS 2002 tool

This is a validated screening tool divided into two parts. The first one assesses the nutritional status based on unintentional weight loss during last 1 to 3 months and food intake during last 1 to 3 weeks. The second part regards the occurrence of diseases or types of treatment which are related to increased daily calories intake (e.g. bone marrow transplant, radio- or chemotherapy). Patients aged 70 and above receive additional score. Nutritional support should be provided if the NRS score is 3 and more. Assessment of nutritional status will be conducted by a nutritionist in the Department of Clinical Nutrition and Dietetics using NRS 2002 tool at baseline, after 4 weeks, and after 12 weeks.

#### EN tolerance

The EN tolerance will be evaluated by the nutritionist in the Department of Clinical Nutrition and Dietetics using own questionnaire including information, such as number of stools, occurrence of nausea, vomiting, abdominal pain, and flatulence. The questionnaire will be filled every day for 12 weeks by patients or their caregivers and evaluated during follow-up visits after 4 and 12 weeks of the study.

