#### Quality of life

Patients’ QOL will be assessed by the nutritionist in the Department of Clinical Nutrition and Dietetics. To assess the patients’ QOL the World Health Organization Quality of Life-BREF (WHOQOL-BREF) questionnaire will be used. It contains questions divided into 4 domains (environmental, psychological, somatic, and social factors). The QOL will be evaluated at baseline, after 4 and 12 weeks.

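### The article gives two timings for enteral nutrition tolerance, and the section that describes the measurement has no baseline: a loss of precision, not of validity

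*Protocol article*

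**What the plan says.** The Methods part of the abstract lists what the trial records, including that "enteral nutrition tolerance as well as quality of life will be measured", and then gives one timetable for the whole list: "Measurements will be obtained at the baseline and after 4 and 12 weeks of treatment".

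The EN tolerance section describes how that measure is obtained. "The questionnaire will be filled every day for 12 weeks by patients or their caregivers", and the forms are "evaluated during follow-up visits after 4 and 12 weeks of the study". No assessment before treatment is mentioned.

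The sections on blood sampling, body composition, NRS 2002 and quality of life each name a baseline. For quality of life, for example: "The QOL will be evaluated at baseline, after 4 and 12 weeks". The Study design section adds a general statement, "The post-allocation clinical and laboratory assessment will be performed at weeks 0, 4, and 12 in all participants", and points to Table 1, which is not shown in the text available.

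The Study aims section speaks of improving tolerance. The Secondary outcomes section defines the outcome as the difference in tolerance between patients on placebo and on probiotic. The Statistical analysis section offers the Mann-Whitney test, Student's t-test and its unequal-variance version, with no covariate.

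**The concern.** The abstract promises a tolerance baseline, and the section that says how tolerance is measured does not provide for one. The diary lasts 12 weeks and so does treatment, which leaves no run-in. Tolerance is the only measure whose own section lacks a baseline, so a site working from that section could reasonably collect nothing before the first capsule.

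At stake is the efficiency of one secondary outcome. The Discussion concedes that the sample is small and non-homogenous, and patients differ in cancer type and feeding access. Symptom burden before treatment is therefore likely to vary widely and to predict symptom burden on treatment. Without a baseline record, that variation stays in the error term and a chance difference between arms cannot be adjusted for. The improvement named in the aim could not be shown within patients at all. A pre-treatment record also cannot be recovered once treatment has begun.

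**Working it through.** The plan states no figure for this outcome, so there is none to reproduce. The check has two parts.

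**1. Text, side by side**

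- Abstract, Methods: tolerance is on the list; times are baseline, week 4 and week 12.
- Study design: clinical assessment in general at weeks 0, 4 and 12; tolerance is not named.
- EN tolerance: daily form over 12 weeks, evaluated at weeks 4 and 12; no baseline.
- Blood sampling, Anthropometric parameters, NRS 2002 tool, Quality of life: baseline named in each.

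The first and third items disagree. The second could cover a tolerance baseline but does not say so.

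**2. What a missing baseline would cost**

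Inputs: 20 per arm (Study design); 16 per arm if the 20% withdrawal in the Statistical analysis section occurs (40 × 0.8 / 2); alpha 0.05 (same section), taken as two-sided; power 80%, as used there for the primary outcome. The correlation ρ between baseline and on-treatment tolerance is assumed at 0.3, 0.5 and 0.7. Differences are in SD units of the tolerance score.

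*Validity.* In 20,000 simulated trials with no treatment effect (normal data, 20 per arm, follow-up-only t-test), the type I error was 0.052 against a nominal 0.05. Leaving out a baseline does not bias the comparison.

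*Chance imbalance.* The standard error of the baseline difference is √(2/n):

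- n = 20: √(2/20) = 0.316 SD. P(|difference| > 0.5 SD) = 2 × [1 − Φ(0.5/0.316)] ≈ 11%.
- n = 16: √(2/16) = 0.354 SD. P ≈ 16%.

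*Precision.* The detectable difference without a baseline is (1.960 + 0.842) × √(2/20) = 0.886 SD by the normal approximation; the t distribution gives 0.909. Baseline adjustment multiplies the variance by 1 − ρ² and the detectable difference by √(1 − ρ²):

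| ρ (assumed) | Variance removed, ρ² | Equivalent sample multiplier, 1/(1 − ρ²) | Detectable difference, 20 per arm |
|---|---|---|---|
| 0 (no baseline) | 0% | 1.00 | 0.886 SD |
| 0.3 | 9% | 1.10 | 0.845 SD |
| 0.5 | 25% | 1.33 | 0.767 SD |
| 0.7 | 49% | 1.96 | 0.633 SD |

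*Adjustment or change score.* A change score has variance 2(1 − ρ) relative to the follow-up value: 1.4, 1.0 and 0.6 at the three correlations. Adjustment gives 0.91, 0.75 and 0.51. Adjustment is better at each, and at ρ = 0.3 a change score would be worse than ignoring the baseline.

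**The case against.** The strongest reply is that the outcome is a between-arm difference in a randomised, double-blind trial. Such a comparison needs no baseline, because its test and interval already allow for chance imbalance. That is correct. A reader might infer that a difference at week 4 or 12 could not be attributed to treatment, or that the tolerance aim could not be answered. The documents do not support this. Only a within-patient reading of improvement needs a baseline.

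A second reply is that a baseline may well be planned: the abstract says so, Study design includes week 0, and Table 1 is not available. This also stands. It would go too far to say that no pre-treatment record exists. What remains is that the section describing the measurement does not agree with the abstract and describes no way to obtain the record.

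A reader might also infer that the trial counts stools and misses diarrhoea, since the items named are "number of stools, occurrence of nausea, vomiting, abdominal pain, and flatulence" and the Background says the frequency of diarrhoea varies "depending on medical condition and the definition of diarrhoea". But the items are introduced as examples, the questionnaire is not reproduced, and an article commonly leaves such detail to the full protocol. Nothing says that mean stool count will be the endpoint, or that patients who leave early will count as symptom-free.

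Finally, the correlations are assumed, and at 0.3 the gain is small. That is fair, and is why a range is shown.

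**Conclusion.** The point holds as an inconsistency with a moderate cost. The abstract and the EN tolerance section disagree on whether tolerance is measured at baseline, and the tests listed in the article make no use of a baseline.

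Followed as the EN tolerance section is written, the plan keeps a valid comparison but forgoes a reduction in variance of about 9 to 49%. The detectable difference at 20 per arm would be about 0.89 SD where 0.85 to 0.63 SD was attainable. An imbalance above 0.5 SD, with a chance of about 11% at 20 per arm and 16% at 16, would go unadjusted.

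These sizes rest on assumed correlations of 0.3 to 0.7, a two-sided alpha, 80% power and a roughly normal score. Symptom-diary data may be skewed, so the figures are illustrative. The matter concerns one secondary outcome and leaves the primary outcome untouched. If Table 1 or the full protocol already schedules a tolerance form before the first capsule, the wording of the EN tolerance section and the adjustment still need attention.

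**What to change.** Make the EN tolerance section agree with the abstract: have the same questionnaire completed at the existing baseline visit, before the first capsule, with a stated recall period. If Table 1 already lists this, say so in the section.

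State that on-treatment tolerance will be compared between arms with adjustment for that baseline, by ANCOVA or, for skewed or count data, a rank-based or count-model equivalent. Prefer this to a change score. Do not use the first diary days as a substitute baseline: they fall within the treatment period, and adjusting for them could remove part of the effect.

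The cost is one form at a visit that already takes place and one covariate in the model. There are three drawbacks. A recalled baseline has more error than a daily diary, which lowers the correlation and so the gain. It is less informative for patients who have only just started enteral feeding, and the article does not say how long patients will have been fed before enrolment. Patients enrolled before the change will have no baseline record, so the analysis needs a stated way to handle them.

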#### Quality of life

Patients’ QOL will be assessed by the nutritionist in the Department of Clinical Nutrition and Dietetics. To assess the patients’ QOL the World Health Organization Quality of Life-BREF (WHOQOL-BREF) questionnaire will be used. It contains questions divided into 4 domains (environmental, psychological, somatic, and social factors). The QOL will be evaluated at baseline, after 4 and 12 weeks.

### Adverse outcomes

Patients are instructed to inform the researchers about any changing conditions during the trial. Furthermore, during follow-up visits the researchers will ask about adverse events which may be related to the intervention. If any adverse events occur it will be noted in report form and reported in publication. However, according to the best of our knowledge, adverse events after administration of *L. plantarum* 299v were not noted.

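### At follow-up visits researchers ask only about adverse events that may be product-related, although spontaneous reporting and recording cover all events; the visit question should be open

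*Protocol article*

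**What the plan says.** The Adverse outcomes section of the protocol article describes harms ascertainment in three steps.

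- Spontaneous reporting: "Patients are instructed to inform the researchers about any changing conditions during the trial". No causal condition is attached.
- Active questioning, introduced as an addition to the first step: "during follow-up visits the researchers will ask about adverse events which may be related to the intervention".
- Recording and reporting: "If any adverse events occur it will be noted in report form and reported in publication". Again no causal condition is attached.

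The section closes with a remark on earlier experience: "according to the best of our knowledge, adverse events after administration of *L. plantarum* 299v were not noted". The Background states that data on the strain are limited "in cancer therapy and no trials about its use in patients with cancer receiving HEN".

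The EN tolerance section describes a separate questionnaire on "number of stools, occurrence of nausea, vomiting, abdominal pain, and flatulence". On its timing: "The questionnaire will be filled every day for 12 weeks by patients or their caregivers".

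**The concern.** The second step is narrower than the first and third. Someone, either the researcher who frames the question or the patient who answers it, must decide whether an event could be due to the capsule before it is mentioned. In a randomised, blinded trial that decision is not needed at this stage, because comparing all events between the arms addresses causality without case-by-case judgement.

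Two features of this trial make the restriction matter. With no earlier trial of the strain in this population, there is no trial evidence for deciding in advance which events could be related. And if the authors know of no adverse events of the strain, a question confined to possibly related events has little defined content. An infection or an admission in a patient with cancer could readily be put down to the disease and go unasked.

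What is at stake is how complete the harms data are, and so how much the comparison of harms between arms can show.

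**Working it through.** The plan gives no figure on this point, so there is none to reproduce. The check sets the statements side by side.

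| Route | Scope | When | Source |
|---|---|---|---|
| Patient volunteers | Any change in condition | Throughout | Adverse outcomes |
| Researcher asks | Events that may be product-related | Weeks 4 and 12 | Adverse outcomes; Participant timeline |
| Event is noted and published | Any adverse event | After it comes to light | Adverse outcomes |
| Daily questionnaire | Stools, nausea, vomiting, abdominal pain, flatulence; any cause | Every day for 12 weeks | EN tolerance |
| Participant does not continue | Data collected and the fact published | When it happens | Participant timeline |

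**Which events can be lost.** Recording is unrestricted, but only an event that has come to light can be recorded. Gastrointestinal symptoms come to light through the questionnaire, and departures from the study through the discontinuation rule. What remains is a non-gastrointestinal event that does not end participation. It comes to light only if the patient volunteers it or the visit question reaches it.

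**Share lost.** For such an event let *v* be the probability that it is volunteered and *r* the probability that it is presumed possibly related and so reached by the question. Assume that the two are independent and that an event asked about is always disclosed. Then the share missed is

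*m* = (1 − *v*)(1 − *r*).

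The documents give neither *v* nor *r*, so *m* is bounded only by 0 (if *v* = 1 or *r* = 1) and 1 (if both are 0). Under the same assumptions an open question sets *r* to 1, and *m* becomes 0 whatever the value of *v*.

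**Effect on the comparison.** The Study design section and the section on allocation and blinding state that researchers and participants are blinded, so take *m* as equal in the two arms. With true risks *p*₁ (probiotic) and *p*₀ (placebo):

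- the observed risks are (1 − *m*)*p*₁ and (1 − *m*)*p*₀;
- the observed difference is (1 − *m*)(*p*₁ − *p*₀), smaller than the true one whenever *m* > 0 and the risks differ;
- the observed ratio is *p*₁/*p*₀, unchanged, but based on fewer events.

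The direction is preserved. The absolute difference and the precision suffer, in a trial with 20 patients per arm. Equality of *m* is an approximation: it could fail if events caused by the product were of a type presumed unrelated more or less often than the background events.

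**The case against.** The strongest reply is that the visit question is only one of several routes and was added to an unrestricted one. Patients are told to report any change, any adverse event is noted and published, bowel and abdominal symptoms are recorded daily, and discontinuations are reported. Blinding prevents the judgement of relatedness from depending on the arm.

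Most of this stands, and it rules out several stronger readings.

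- A reader might infer that harms are filtered before they are recorded, so that the trial keeps a log of related events only. The recording sentence has no such condition; the restriction is on what is asked.
- A reader might infer that deaths drop out of the comparison. On a plain reading, the discontinuation rule in Participant timeline brings deaths and withdrawals to light.
- A reader might treat the closing remark about earlier experience as the basis for a planned safety conclusion. It is a hedged statement of what the authors know, and neither the aims nor the outcomes include a safety objective.
- A reader might use a zero-event confidence limit for 20 patients to size the problem. That limit follows from the sample size under complete capture and would be the same after the wording was changed.

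The reply does not close the gap. An event that is neither asked about nor volunteered cannot be noted. Reliance on what patients report from home is also something the authors themselves treat with caution: the limitations in the Discussion say that they cannot be sure the questionnaire is completed daily rather than just before visits.

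Nor does the condensed form of an article excuse the sentence, because it states a rule. By contrast, definitions of seriousness, onset dates, a safety population and the layout of tables are commonly left to the full protocol or analysis plan and are not criticised here.

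**Conclusion.** The point holds as an inconsistency of scope within one section: any change is to be volunteered, only possibly related events are asked about, and any event is recorded. The likely consequence is under-ascertainment of non-gastrointestinal events that are presumed unrelated and not volunteered. Given blinding, this should affect both arms about equally and attenuate the difference in harms rather than favour one arm.

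The size cannot be stated, because it depends on how often such events are volunteered and how often they are presumed related, and the documents say nothing on either. The conclusion rests on reading the visit sentence as written and on blinding being maintained. It does not touch the primary outcome. It is a cheap improvement worth making, because the article promises to publish the adverse events.

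**What to change.** Replace the visit sentence in Adverse outcomes with wording to this effect: *At each follow-up visit the researchers will put an open question about every adverse event since the previous visit, whatever its presumed cause. All events will be recorded, and their relation to the study product will be judged afterwards, while treatment allocation is still blinded.* This brings the question into line with the spontaneous reporting and recording sentences, which can stay as they are.

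The cost is one changed sentence and slightly more time at the two existing follow-up visits. No extra visit is needed. The downside is a longer list of events, many of them unrelated to the product, to be recorded and assessed.
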